## Results

This study is expected to provide insights into whether there is an association between household livestock ownership (measured by TLU index) and the prevalence of childhood stunting and wasting in central rural India. This study will be conducted from October 2025 to September 2026. Currently, necessary approvals are obtained, and data collection is planned to begin from November 2025 to May 2026.

## Discussion

### Overview

The research aim of this study is to determine the association between stunting among children younger than 5 years and household livestock ownership in rural areas of central India, and if a one-health approach can contribute to and address this association.

According to Hossain and Khan [22], owning cattle in Bangladesh is substantially associated with a lower incidence of stunting. The beneficial impact of owning a domestic animal on the decrease in stunting in children implies that apart from nutritional interventions in Bangladesh, enhancing livestock output could also aid in enhancing the nutritional condition of children. To maximize the effect, integrated programs, including agricultural production and WASH, are needed. A small effect size may be owing to the lack of dietary diversity, livestock health, and productivity data as well as the complexity of the relationship, requiring further studies [22].

Another study by Gelli et al [23] showed that the size of the chicken flock, poultry husbandry, and household hygiene standards were all correlated with the occurrence of chicken feces. Higher height-for-age *z* scores were linked to improved water sources and more visibly clean children. Lower weight-for-height *z* scores were linked to the presence of chicken feces; no correlations were detected with the height-for-age *z* scores. They also concluded that increasing poultry production in environments where children and poultry coexist may raise nutrition-related risks for young children, and more livestock-focused WASH programs may act as a significant barrier to stopping the spread of pathogens from livestock to humans [23].

A systematic review by Muema et al [24] suggested that depending on the type of intervention and length of program/intervention implementation, different livestock interventions have different effects on stunting, wasting, and underweight. Hence, due to the heterogeneity in reporting metrics, they were unable to compute the pool estimates. They further suggested that more randomized controlled trials with uniform and comparable reporting criteria are therefore required to strengthen the body of information regarding the effects of nutrition-sensitive livestock interventions on child development outcomes because the quality of the available data is low. They concluded that improving dietary diversity was a result of nutrition-sensitive livestock interventions, which increased the consumption of animal-source food [24].

Mosites et al [25] incorporated monthly anthropometric measurements for children younger than 5 years into an ongoing linked human and animal surveillance cohort in Western Kenya. Using linear mixed models, they tested whether baseline household livestock ownership was related to baseline child height-for-age or prospective growth rate. This study did not find a relationship between owning higher numbers of household livestock and child baseline anthropometric measures or subsequent child linear growth outcomes. However, there was an indication that livestock disease was associated with some measures of diminished growth [25].

### Limitations

Potential limitations that can impact the validity and reliability of the findings are as follows. Selection bias, the method of selecting cases and controls, may not accurately reflect the general population, leading to possible bias in the findings. Recall bias can be another limitation in this study, as this study will rely on the informant’s recollection of livestock ownership and child health history. Failure to consider the confounding factors can misrepresent the true association, adding to the limitations. Inaccuracies in anthropometry measurements of children can affect the study findings. Our findings will be from a specific region in central rural India, which may not be generalized to other regions with different cultural, environmental, and economic settings.

### Conclusions

There is a lack of studies in Maharashtra, India, which examine the relationship between livestock ownership and stunting in children younger than 5 years. Considering existing research gaps, this study aims to assess the relationship between stunting among children younger than 5 years in central rural India and livestock ownership by using the TLU index. It will determine the prevalence of the current stunting, wasting, and underweight among Indian children younger than 5 years. This study will offer insight into the correlations between stunting, wasting, and livestock ownership. This association will guide policymakers and program designers about the potential strategies to reduce stunting, such as promoting livestock ownership and ensuring that it provides nutritional benefits for children. This will be crucial in developing new public health policies, integrated programs, and nutritional interventions. It will also offer insights into how household resources (like livestock) are allocated and their impact on child nutrition and health, contributing to broader discussions about rural livelihoods and child development, particularly in a resource-constrained rural settings where understanding the determinants of child health is critical for developing effective interventions. It will help to generate hypotheses about the pathways through which livestock ownership might influence stunting, which can then be tested in future research such as cohort or interventional studies.

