**Conclusions:**

Our findings will show the prevalence of the current stunting, wasting, and underweight rates among Indian children younger than 5 years and the association of these rates with livestock ownership by using the TLU index. These results will be instrumental in building new public health policies, integrated programs, and nutritional interventions.

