## Methods

### Study Design, Participants, and Setting

This case-control study will be conducted in a community-based setting. It will be performed for 24 months in a few randomly selected villages from 8 rural blocks of Wardha district, located in central Maharashtra, by using a computerized method. Cases and controls will be proportionally allocated based on the number of children younger than 5 years and the stunting prevalence in each block. Permission for the interviews will be obtained from the authority/sarpanch of the respective villages. The list of children younger than 5 years of the selected blocks will be acquired from the respective Anganwadi Center of the village. For each case, 1 control will be recruited through simple random sampling. Informants will be briefed on the study’s process and purpose. Participation will only be allowed after either parent gives written and informed consent. Data will be gathered using a semistructured questionnaire in English/Marathi via interviews. The questionnaire was developed and reviewed by field experts and will be validated through a pilot study (Multimedia Appendix 1). An infantometer/stadiometer will be used by the investigator to measure the length/height (in centimeters), and weighing scales will be used to measure the weight (in kilograms) of each child. The children’s height and weight measurements will be compared to WHO 2006 standards based on age and gender to calculate the height-for-age *z* score and weight-for-height *z* score. Stunting and wasting are defined as falling below –2 SD of the WHO reference median. After plotting the measurements on the WHO growth charts, stunted and nonstunted children will be listed separately. All stunted children will be the cases in this study, and all nonstunted children will be the controls.

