### Sample Size

The study will involve participants chosen based on specific inclusion and exclusion criteria. It will include all children younger than 5 years from the respective villages. Considering the overall number of children younger than 5 years in the Wardha rural area sample, the total population was 88,224 children [20].

Estimated sample size = n≥(NZ_(1-α⁄2)^2 p(1-p))/(d^2 (N-1)+Z_(1-α⁄2)^2 p(1-p)), where α (a)=.05; estimated proportion of children younger than 5 years who are stunted (height-for-age) *P*=.28 [9]; and estimation error (d) = 5% = 0.05. The minimal sample size calculated for this study will be 614, of which 307 are cases and 307 are controls, considering the ratio of case-control is 1:1.

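### The two Conclusions sections promise the prevalence of stunting, wasting and underweight in Indian children, but a sample taken 1:1 on stunting status shows 50% stunting whatever the true rate

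*Protocol article*

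**What the plan says.** The promise appears twice. The Conclusions section of the Discussion says: "It will determine the prevalence of the current stunting, wasting, and underweight among Indian children younger than 5 years". The Conclusions paragraph of the abstract says: "Our findings will show the prevalence of the current stunting, wasting, and underweight rates among Indian children younger than 5 years".

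The design is set out in Study Design, Participants, and Setting: "This case-control study will be conducted in a community-based setting". Children are measured, plotted on the WHO charts and listed by stunting status. Stunted children are the cases and nonstunted children the controls. On control selection: "For each case, 1 control will be recruited through simple random sampling". The Sample Size section fixes the numbers; the minimum "will be 614, of which 307 are cases and 307 are controls, considering the ratio of case-control is 1:1".

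The Data Analysis section plans comparisons of stunted with nonstunted children and multivariable logistic regression. The Limitations section says the findings come from one region, "which may not be generalized to other regions" with different settings, and that the selection of cases and controls may not reflect the general population.

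**The concern.** When sampling is on the outcome at a fixed ratio, the investigator sets the share of the sample with that outcome. The 614 children then carry no information about how common stunting is. Wasting and underweight are not fixed in this way, but stunted children are over-represented, so crude rates of anything associated with stunting are pulled towards the rate in stunted children.

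The two Conclusions sections offer the findings as a basis for public health policy. Prevalences read straight off the 614 would be wrong for stunting and probably too high for underweight. They would also be attributed to a national population that was not sampled.

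**Working it through.** **1. The plan's own sample size.** The Sample Size section uses n = N·Z²·p(1−p) / [d²(N−1) + Z²·p(1−p)], with N = 88,224, Z = 1.96 (α = 0.05), p = 0.28 and d = 0.05.

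- Z²·p(1−p) = 3.8416 × 0.28 × 0.72 = 0.7745.
- n = 88,224 × 0.7745 / (0.0025 × 88,223 + 0.7745) = 68,326.5 / 221.33 = 308.7.

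This rounds up to 309 per group, or 618 in all. The stated 307 and 614 agree closely enough. So 614 is a single-proportion precision figure doubled for the 1:1 ratio.

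**2. Stunting in the 614.** Cases / (cases + controls) = 307/614 = 50.0%, whatever the population rate. The protocol expects 28% (Sample Size) or 29.4% (Introduction, rural Wardha). A simple random sample of 614 would hold about 614 × 0.28 = 172 or 614 × 0.294 = 181 stunted children, not 307. This step needs no assumption.

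**3. Wasting and underweight in the 614.** Let w1 and w0 be the rates in stunted and nonstunted children, p the population stunting rate and W the overall rate. For an assumed odds ratio, solve p·w1 + (1−p)·w0 = W. The crude rate in the 1:1 sample is (w1 + w0)/2. Inputs from the Introduction are wasting 25.8% (rural Wardha) and underweight 35.5% (national; no Wardha figure is given). p = 0.28. The odds ratios are assumptions, because the protocol gives none.

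| Outcome | True rate | Assumed OR with stunting | w0 | w1 | Crude rate in the 614 |
|---|---|---|---|---|---|
| Wasting | 25.8% | 1 | 25.8% | 25.8% | 25.8% |
| Wasting | 25.8% | 1.5 | 23.5% | 31.6% | 27.6% |
| Wasting | 25.8% | 2 | 21.9% | 35.9% | 28.9% |
| Underweight | 35.5% | 1 | 35.5% | 35.5% | 35.5% |
| Underweight | 35.5% | 4 | 26.4% | 58.9% | 42.7% |
| Underweight | 35.5% | 10 | 21.0% | 72.7% | 46.9% |

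With p = 0.294 instead, the crude values are up to 0.2 points lower for wasting and up to 0.8 points lower for underweight.

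Weighting cases by p and controls by 1−p returns the true rates. But p has to come from outside the 614.

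**4. A denominator that could serve.** To find 307 stunted children, about 307/0.294 = 1,044 to 307/0.28 = 1,097 children must be measured. If all of them are measured before controls are drawn, that set can give prevalence. The article states neither the number measured nor that prevalence will be taken from that set.

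**5. Target population.** Villages come from rural blocks of one district, and eligibility starts at 6 months with health and residence exclusions. The claim covers all Indian children under 5 years, and the Limitations section argues against extending it that far.

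**The case against.** The strongest reply is that the prevalence claim need not come from the 614. The design section has children measured and listed by stunting status, and the Sample Size section says that all children under 5 in the villages will be included. A wider measured list is a possible reading. That stands as a route to a remedy. It does not rescue the text: the abstract describes a study among 614 children, the statement about all children conflicts with a fixed 1:1 sample, and no prevalence denominator is stated. A condensed article may leave an estimator or weights to a fuller plan, so their absence is not the complaint. The complaint is a positive claim that the stated sampling cannot deliver.

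A second reply is that prevalence is not the objective. This is correct. The objective and the Data Analysis section concern association, and 1:1 sampling does not damage the stunting-livestock odds ratio.

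Three stronger readings are tempting and are not supported:

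- A reader might take the Results section as a third prevalence promise, since it mentions "the prevalence of childhood stunting and wasting in central rural India". The full sentence concerns an association with livestock ownership, not a prevalence estimate.
- A reader might infer that the wasting figures would be seriously wrong. At the assumed odds ratios the shift is about 2 to 3 points, inside the plan's own 5-point estimation error. The protocol also lacks the inputs to show any material bias in a wasting-livestock odds ratio.
- A reader might infer that underweight cannot be measured, because only height-for-age and weight-for-height scores are named. Weight and age are recorded, so weight-for-age can be derived.

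**Conclusion.** The concern holds for the prevalence claim in the two Conclusions sections. For stunting the contradiction is certain: 50% by construction against an expected 28% to 29.4%, an excess of about 21 to 22 points. For underweight the crude figure would be some 7 to 11 points too high if the odds ratio with stunting lies between 4 and 10. For wasting it would be about 2 to 3 points too high at odds ratios of 1.5 to 2. Both results rest on assumed odds ratios and vanish at OR 1; the underweight result also combines a national rate with the 28% stunting assumed for Wardha. The reference to Indian children contradicts the protocol's own limitation.

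This should be corrected, but it is not critical. A reader might infer that the study as a whole is invalid. The documents do not support that, because the claim stands outside the objective and the planned analysis, and the main odds ratio is intact.

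**What to change.** **Simplest change.** Delete the prevalence claim from the Conclusions sections of the abstract and the Discussion. The cost is two sentences.

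**If prevalence is to be kept:**

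- State that it will be estimated only from the full set of eligible children measured before controls are sampled, about 1,044 to 1,097 if 307 cases are to be found.
- Measure every eligible listed child in the selected villages, and record and keep the number measured along with all measurements.
- Weight for the allocation across blocks, which depends on child numbers and stunting prevalence, and give village-clustered confidence intervals.
- Compute weight-for-age from the weight and age already collected.
- Limit the claim to eligible children aged 6-59 months in the sampled rural areas of Wardha.
- Reconcile the statement that all children under 5 in the villages will be included with the fixed sample of 614.

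This costs some wording, retention of the screening data and a modest extra analysis, plus added fieldwork if measuring every eligible child was not already intended. It has to be settled before data collection, planned from November 2025, because the 614 alone cannot supply the weights afterwards.

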## Appendix

Multimedia Appendix 1 Study questionnaire.

## Abbreviations

NFHS-5: National Family Health Survey
TLU: Tropical Livestock Unit
WASH: Water, Sanitation, and Hygiene
WHO: World Health Organization
